**Study protocol**

1. Study Type.

1.1. Single-center, three-year cross-sectional study in patients with rheumatoid arthritis (RA), systemic lupus erythematosus (SLE), and controls to estimate the relationships between serum expression and gene signature of type I, II, and III interferons (and subtypes) and carotid intima-media thickness, plaque presence, and carotid stiffness in patients with RA, SLE, and controls. Additionally, this study will assess the relationship between alterations in serum and gene expression with other cardiovascular disease determinants such as lipid profile, insulin resistance, beta cell dysfunction, reverse cholesterol transport, etc.

1.2. A six-month prospective study in a subgroup of RA patients initiating anti-TNF therapies. Eligible patients starting anti-TNF therapy will be studied before and after six months of treatment. We will determine if the modifications in IFN molecule levels and expression change after treatment and if changes also occur in lipid profile and insulin resistance associated with potential changes in IFN. Ultrasound techniques will not be performed during this second visit on these patients.

1.3. Variables.

1.3.1. Primary outcome variable (dependent): carotid artery intima-media thickness and plaque presence, carotid stiffness measurement (endothelial dysfunction); reverse cholesterol transport; insulin resistance and beta cell dysfunction.

1.3.2. Secondary variables: explanatory (independent) variables: serum concentrations and gene expression of IFN types I, II, and III and subtypes. Other dependent variables: a) abnormal lipid profile including paraoxonase/arylesterase and myeloperoxidase antioxidant activity, cholesterol ester transfer protein activity, lecithin-cholesterol acyltransferase, reverse cholesterol transport measurements, PCSK9 (Proprotein Convertase Subtilisin/Kexin Type 9) levels; b) insulin resistance indices and beta cell function (measured via serum insulin and C-peptide and calculated using HOMA2 – homeostatic model assessment). Confounding variables: sex, age, body mass index, obesity, blood pressure, antihypertensive treatment, fasting glucose, presence of diabetes, smoking, statin use.

Demographic data, surgical history, smoking, vascular comorbidities, and current treatment will be recorded. Weight and height will be measured to determine body mass index (BMI) (body weight divided by height squared in kg/m2) and waist-to-hip ratio. Disease activity will be assessed using DAS28 (Disease Activity Score 28 Joints), CDAI (Clinical Disease Activity Index), or SDAI (Simple Disease Activity Index), and HAQ (Health Assessment Questionnaire). Metabolic syndrome will be defined following the 2005 National Cholesterol Education Program Adult Treatment Panel III (ATP III) criteria. Cardiovascular risk in the Spanish population will be assessed via the SCORE2 (Systematic Coronary Risk Evaluation version 2 updated). Disease activity and damage in SLE will be evaluated through the Systemic Lupus Erythematosus Disease Activity Index (SLEDAI-2K) and the SLICC/ACR damage index (SDI), respectively. Disease severity will also be assessed by the Katz index.

2. Population Selection

2.1. Inclusion Criteria: 1. Men or women not pregnant or breastfeeding; 2. ≥18 years and <70 years old; 3. Patients under any disease-modifying drug treatment (including those already receiving biologicals) or initiating biological treatment (anti-TNF or others); 4. If receiving oral corticosteroids, dose must be ≤ 10 mg prednisone and stable for at least one month prior to inclusion; 5. Patients capable and willing to sign informed consent.

2.2. Exclusion Criteria: Patients with any of the following will be ineligible: 1. Autoimmune rheumatic diseases other than RA or SLE, such as mixed connective tissue disease, scleroderma, polymyositis, or systemic involvement secondary to RA (e.g., vasculitis, pulmonary fibrosis, or Felty’s syndrome). Sjögren’s syndrome with RA or SLE is not an exclusion criterion; 2. Functional Class IV RA as defined by the ACR Functional Status Classification (complete or substantial disability confining the patient to bed or wheelchair with inability for self-care). 3. History or current presence of inflammatory joint disease other than RA (e.g., gout, reactive arthritis, psoriatic arthritis, seronegative spondyloarthropathy, Lyme disease). 4. Glomerular filtration rate under 60 ml/min/1.73 m2 and presence of active renal disease. 5. Pregnant or lactating women. 6. Evidence of uncontrolled severe concomitant cardiovascular, nervous system, pulmonary (including COPD), renal, hepatic, endocrine (including diabetes mellitus), or gastrointestinal diseases, or any which, in the investigator’s judgment, would alter the interferon system profile. 7. Body weight >150 kg or BMI >50 kg/m2. 8. History of alcoholism, drug addiction or substance abuse within six months prior to screening visit.

3.. Data Collection

3.1. Baseline. Data for each patient will be recorded in a Case Report Form (CRF) in paper and electronic formats. CRF data must be verifiable against source documents such as clinical histories, laboratory data, and ultrasound reports. Concentrations obtained by the different assays will be attached to each patient’s CRF with standard curves and validation criteria. The data will be included in an electronic database facilitating statistical analysis. Blood samples will be collected fasting from the antecubital vein during patient and control study visits.

3.2. Carotid Intima-Media Thickness and Plaque Evaluation. Carotid ultrasound will evaluate the thickness of the carotid intima-media (cIMT) in the common carotid artery and detect focal plaques within the extracranial carotid tree in patients and controls. A commercially available ultrasound system, Mylab 70, Esaote (Genoa, Italy), equipped with a 7-12 MHz linear transducer and automated radiofrequency-guided software–Quality Intima Media Thickness Real-Time (QIMT, Esaote, Maastricht, Netherlands)–will be used. Plaque criteria in accessible extracranial carotid tree segments (common carotid artery, bulb, and internal carotid artery) will be based on Mannheim consensus.

3.3. Arterial Stiffness Evaluation. Arterial stiffness will be assessed by ultrasound exam using Mylab 70 (Esaote) equipped with an automatic Quality Arterial Stiffness (QAS) radiofrequency (RF) package and a LA523 vascular probe of 4-13 MHz with RF emission-reception signals. QAS automatically evaluates changes in arterial internal diameter between systolic and diastolic phases, obtaining arterial distension waveform via real-time automatic RF signal analysis. This enables calculation of arterial stiffness and arterial wall stress (pulse wave velocity, PWV in m/s, and augmentation index, AIX)–carotid arterial stiffness index.

3.4. Follow-up Data Collection. A subgroup of patients requiring anti-TNF treatment will be recruited at our Day Hospital for inclusion. Initial visits for these patients will be similar to the case-control study visit schedules. Patients continuing anti-TNF treatment at 6 months will undergo repeated analytical parameter determination.

4. Immunoassays for IFN-induced soluble proteins and IFN-stimulated gene assays. Laboratory techniques for IFN analysis are detailed in the Annex of this submission.

5. Data Analysis Objectives. IFN gene expression scores are typically categorized (low, medium, high), but we will explore continuous and categorical IFN score analysis. Initially, multivariable analyses will compare IFN expression between patients with RA and SLE and controls. The relationship between IFN expression and carotid plaque presence, intima-media thickness, or arterial stiffness will be evaluated using multivariable linear or logistic regression. Differences in IFN effects on atheromatosis or carotid stiffness between diseases or between groups and controls will be assessed by adding interaction terms to regression models to determine if relationships differ among the three populations (RA, SLE, controls). A predictive model will be developed for interferon system molecules that, parsimoniously combined, predict carotid plaque presence or endothelial dysfunction. The relationship between IFN and other cardiovascular risk factors will be studied by multivariable linear/logistic regression. Stata 17 will be used for analysis; statistical significance is defined as a two-sided p-value <0.05.

6. Ethics. The project will be submitted to the Ethics Committee of our center. No patient or control will experience any change in care from the Rheumatology Department. Patients and controls will sign informed consent and will receive a study information sheet outlining objectives and interventions. The processing, communication, and transfer of all participants’ personal data are detailed in this application.

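### Carotid stiffness is labelled endothelial dysfunction in a primary outcome and a prediction target, but the described procedures measure only arterial structure and wall mechanics

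*Protocol*

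**What the plan says.** Section 1.3.1 of the protocol gives the primary outcomes. One of them is "carotid stiffness measurement (endothelial dysfunction", where the term in brackets explains the stiffness measurement.

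Section 3.3 describes the examination behind that outcome. Radiofrequency ultrasound is used, and "QAS automatically evaluates changes in arterial internal diameter between systolic and diastolic phases". From the resulting waveform, "This enables calculation of arterial stiffness and arterial wall stress (pulse wave velocity, PWV in m/s, and augmentation index, AIX"; a carotid stiffness index is named as well. Section 3.2 covers the other vascular examination: "Carotid ultrasound will evaluate the thickness of the carotid intima-media (cIMT) in the common carotid artery and detect focal plaques".

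Section 5 uses two names for the outcome. For the association analysis it is stiffness: "The relationship between IFN expression and carotid plaque presence, intima-media thickness, or arterial stiffness will be evaluated using multivariable linear or logistic regression". The interaction analysis also speaks of carotid stiffness, as does the study aim in section 1.1. For the predictive model, section 5 looks for interferon molecules that, "parsimoniously combined, predict carotid plaque presence or endothelial dysfunction". The word stiffness does not occur in that sentence, and endothelial dysfunction has no definition other than the bracket in section 1.3.1.

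**The concern.** Stiffness indices describe how the arterial wall behaves mechanically as pressure rises and falls over the cardiac cycle. Endothelial function is a different property. The two may be correlated, but a reading of one is not a measurement of the other. Wall mechanics also reflect other influences, such as age and blood pressure, both of which section 1.3.2 lists as confounders.

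What is at stake is the claim the study can make. If the wording is followed, a positive result for the stiffness outcome can be written up as interferon predicting endothelial dysfunction, and a null result as evidence that it does not. Neither statement follows from the data the protocol describes. Section 8 stresses the role of interferon and of related new therapies, so a mechanistic claim under the wrong name would carry weight with readers.

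**Working it through.** No arithmetic applies. The protocol gives no sample size, event count or effect size tied to this outcome, so there is no figure to reproduce. The check sets label, measurement and analysis target side by side.

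**1. Where the term occurs.** Endothelial dysfunction appears twice in the protocol: as the gloss on stiffness in section 1.3.1 and as a model target in section 5.

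**2. What is measured.**

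| Section | Reading | What it describes |
|---|---|---|
| 3.2 | Intima-media thickness | Wall structure |
| 3.2 | Plaque | Wall structure |
| 3.3 | Diameter change between systole and diastole | Wall mechanics |
| 3.3 | Pulse wave velocity, augmentation index, stiffness index | Wall mechanics |

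None of these rows is a test of endothelial function. The protocol describes no vasodilator stimulus and no vascular reactivity test. The laboratory outcomes in section 1.3.2 are grouped under lipid profile or under insulin resistance and beta-cell function; none is presented as an endothelial marker.

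**3. Could the measurement be described elsewhere?** The Annex is not shown. Section 4 says of it: "Laboratory techniques for IFN analysis are detailed in the Annex of this submission". Section 7 adds the SiMOA technique and principal component analysis for the interferon signature. An endothelial test there is unlikely on that description, though it cannot be excluded.

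**4. What name each part of the plan uses.**

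| Place | Name |
|---|---|
| 1.1, aim | Carotid stiffness |
| 1.3.1, primary outcome | Carotid stiffness, glossed as endothelial dysfunction |
| 3.3, procedure | Arterial stiffness |
| 5, association analysis | Arterial stiffness |
| 5, interaction analysis | Carotid stiffness |
| 5, predictive model | Endothelial dysfunction |

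**5. Reading the tables together.** A single set of ultrasound readings carries two names that denote different constructs. The name without a measurement behind it stands alone as a prediction target. Because section 1.3.1 ties the term to stiffness, the model can still be fitted. What cannot be done is to carry its result over to endothelial function.

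**6. Extent.** The primary outcomes in section 1.3.1 number six when listed singly: intima-media thickness, plaque, stiffness, reverse cholesterol transport, insulin resistance and beta-cell dysfunction. One of the six is affected. The predictive model has two targets, plaque and endothelial dysfunction; one of the two is affected.

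**The case against.** The strongest reply is that the bracket in section 1.3.1 works as a definition. A reader who follows it knows what will be measured and modelled, and the aim, the procedure and most of the analysis section say stiffness plainly. On this view only a word is wrong, no estimate or test changes, and worry about how results will be reported is a guess about a future paper. Much of this stands. The analyses are feasible, stiffness results reported as stiffness are sound, and plaque, the first-named prediction target, is untouched. It is also true that the distinction between stiffness and endothelial function is a general measurement point that the protocol does not itself discuss. But the reply does not remove the problem. The prediction sentence in section 5 states the target in its own right as endothelial dysfunction, so the plan itself, and not only some later report, names a construct that the described procedures do not observe.

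A reader might go further and infer that a present/absent target forces stiffness to be dichotomised, with a loss of information. The documents do not support that. In "predict carotid plaque presence or endothelial dysfunction" the word for presence belongs to plaque. No cut-off or split of stiffness is stated anywhere, and linear regression is among the planned methods. The low, medium and high categories in section 5 concern interferon scores, which are explanatory variables, and continuous analysis of them is planned too.

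A reader might also infer that pulse wave velocity ought to be singled out as the stiffness measure. Section 3.3 lists several indices, and correcting the label does not require choosing among them.

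**Conclusion.** The point holds as a mismatch between a label and what is measured. The procedures described support conclusions about carotid stiffness, intima-media thickness and plaque. They do not support a conclusion about endothelial function, positive or null. The mismatch sits in two places in the text and has no numerical size: no power, precision or error rate is altered. It deserves correction because it concerns what a primary outcome and a model target are said to be, which is more than a slip in background text.

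Two assumptions carry this conclusion. The first is the general one that wall stiffness is not itself a measure of endothelial function. The second is that the unseen Annex contains no endothelial test, which its described scope makes likely. It would be too strong to say that the stiffness analyses are invalid or that the predictive model cannot be built; neither follows from the protocol.

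**What to change.** In section 1.3.1, delete the bracketed gloss and name the outcome carotid stiffness, referring to the indices already listed in section 3.3. In the prediction sentence of section 5, replace endothelial dysfunction with carotid stiffness, so that the two targets are plaque presence and carotid stiffness. Limit the conclusions drawn from these analyses to stiffness. If endothelial function is truly the construct intended, a measure of it has to be specified, which would be a change of procedure and not of wording.

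Renaming costs no visit, sample or examination, and leaves the planned regressions as they are. The downside is a narrower claim: the study would speak about interferon and arterial stiffness, and could raise endothelial dysfunction only as a possible explanation.

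### The confounder list in Protocol 1.3.2 names statins as the only lipid drug and no glucose-lowering treatment, although PCSK9, lipid function and insulin measures are outcomes

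*Protocol*

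**What the plan says.** Protocol 1.3.2 lists among its dependent variables "abnormal lipid profile including paraoxonase/arylesterase and myeloperoxidase antioxidant activity, cholesterol ester transfer protein activity, lecithin-cholesterol acyltransferase, reverse cholesterol transport measurements" and "PCSK9 (Proprotein Convertase Subtilisin/Kexin Type 9) levels", and then insulin resistance and beta-cell indices calculated with HOMA2. Section 1.3.1 also places "reverse cholesterol transport; insulin resistance and beta cell dysfunction" among the primary outcomes. PCSK9 is therefore purely secondary, but part of the lipid and insulin group is not.

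The adjustment set is written out in 1.3.2: "Confounding variables: sex, age, body mass index, obesity, blood pressure, antihypertensive treatment, fasting glucose, presence of diabetes, smoking, statin use".

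On eligibility, section 2.1 admits "Patients under any disease-modifying drug treatment (including those already receiving biologicals") and limits oral corticosteroids, but does not mention lipid-lowering or glucose-lowering drugs. The exclusions in 2.2 do not mention them either. The nearest is exclusion 6. It covers uncontrolled severe disease, diabetes included, and conditions that "in the investigator’s judgment, would alter the interferon system profile".

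The paragraph on clinical assessments that follows 1.3.2 says that "vascular comorbidities, and current treatment will be recorded". Section 5 plans multivariable regression for the relation of IFN to the other cardiovascular risk factors and names no further covariates.

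**The concern.** The list treats its three drug-sensitive domains unevenly. For blood pressure it has both the level and the whole class of treatment. For lipids it has one drug type. For glucose it has fasting glucose and diabetes status, but no treatment. By listing statin use the protocol accepts that lipid treatment can confound these relationships, yet it leaves out the rest of that treatment.

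The gap is most direct for PCSK9: a drug that acts on PCSK9 alters the quantity being assayed, almost by definition. For insulin resistance and beta-cell function, diabetes that is not both severe and uncontrolled remains eligible, and the list itself expects some participants with diabetes. A yes/no diabetes term cannot separate treated from untreated diabetes.

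At stake are the IFN coefficients for these outcomes and the comparisons among RA, SLE and controls. Both could absorb a treatment effect if treatment is spread unevenly over IFN levels or groups.

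**Working it through.** The protocol gives no sample size, standard deviation, effect size or share of users for these outcomes, so there is no figure to reproduce. The check is a sensitivity calculation in which every input is assumed.

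**Inputs (all assumed)**
- p: share of participants on the omitted treatment, 0 to 10%.
- δ: shift in the outcome among users, 0.5 to 3 outcome SDs.
- d: difference in IFN between users and non-users, 0 to 0.5 SD.

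**1. Bias in the IFN slope**, in outcome SDs per SD of IFN: δ·p(1−p)·d / (1 + p(1−p)·d²).
- p = 0 or d = 0: bias 0.
- p = 1%, δ = 1, d = 0.25: 0.0099 × 0.25 / 1.0006 = 0.0025.
- p = 5%, δ = 3, d = 0.5: 3 × 0.0475 × 0.5 / 1.0119 = 0.070.
- p = 10%, δ = 3, d = 0.5: 3 × 0.09 × 0.5 / 1.0225 = 0.132.

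**2. Bias in a group difference**: δ × (share in patients − share in controls).
- No difference in use: 0.
- Difference of 1 percentage point, δ = 1 to 3: 0.01 to 0.03 SD.
- Difference of 10 percentage points, δ = 1 to 3: 0.10 to 0.30 SD.

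**3. Noise when use is unrelated to IFN and group**: residual SD multiplied by √(1 + δ²·p(1−p)).
- δ = 3, p = 1%: √(1 + 9 × 0.0099) = 1.044, a rise of 4%.
- δ = 3, p = 10%: √(1 + 9 × 0.09) = 1.345, a rise of 34%.

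**4. PCSK9 in particular.** Assume a coefficient of variation of 35% in untreated participants and a level k times as high in treated ones. On the untransformed scale the SD is multiplied by √(1 + p(1−p)·((k−1)/0.35)²). With p = 1%:
- k = 0.3: √(1 + 0.0099 × 4) = 1.02.
- k = 3: √(1 + 0.0099 × 32.65) = 1.15.
- k = 5: √(1 + 0.0099 × 130.6) = 1.51.
- k = 8: √(1 + 0.0099 × 400) = 2.23.

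With p = 2%, k = 3, 5 and 8 give 1.28, 1.89 and 2.97. On the log scale the same coefficient of variation is a log SD of √ln(1 + 0.35²) = 0.34. With p = 1%, the multipliers for k = 3, 5 and 8 are then only 1.05, 1.11 and 1.17. The PCSK9 result therefore depends heavily on the direction and size of the drug effect and on whether the outcome is transformed.

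No separate size was calculated for glucose-lowering treatment. The formulas in steps 1 to 3 apply in the same way, but the diabetes and fasting-glucose terms already in the list may take up part of any effect.

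**The case against.** A reader might infer that users of PCSK9-directed drugs are in the study and that the PCSK9 and lipid results do measure other treatments. The documents do not support that. They do not say that any participant takes a non-statin lipid drug; they only fail to exclude such users, and possibly none will be enrolled. Even with users present, the IFN coefficient is biased only if use is related to IFN or to group.

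A reader might also take the multipliers from 1.15 to 2.97 as the expected damage. They describe loss of precision, not confounding. They need a several-fold rise in PCSK9 on an untransformed scale, and neither the 35% nor k comes from the protocol.

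The protocol also does not say that drugs such as ezetimibe or fibrates change these particular lipid measures. For them the argument rests on the protocol's own decision to treat statin use as a confounder; only for drugs acting on PCSK9 itself is the effect close to definitional.

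Finally, covariate coding and sensitivity analyses are often left to the SAP, which is not shown, and section 5 does not confine the models to the list in 1.3.2. That lowers the weight of the point but does not remove it. The protocol has chosen to write out its confounders, and a SAP that follows them takes over the gap.

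Replacing statin use by a full set of class terms would go too far: if use is rare, some cells would be nearly empty.

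**Conclusion.** The point holds as a gap in a stated list. Section 1.3.2 adjusts for one lipid drug type and no glucose-lowering treatment, while PCSK9, lipid function, insulin resistance and beta-cell function are outcomes and users of the other drugs are not excluded. If such users are enrolled, the results for these outcomes may partly reflect treatment.

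The effect runs from nil to material, and the documents do not locate it in that range. It is nil with no users. With use unrelated to IFN and group it is loss of precision only. It reaches the upper values in the working only if 10% of participants are users (or use differs by 10 percentage points between groups) and the outcome shifts by 3 SDs. The correction is worth making because it is cheap, some of the affected outcomes are primary, and fixing the rule before the data are seen avoids a post hoc decision about a few influential participants.

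**What to change.** In Protocol 1.3.2:
- Keep statin use and add other lipid-lowering treatment (yes/no), split by class only where numbers allow.
- State that participants on PCSK9-directed drugs are left out of the PCSK9 analysis, and that the other lipid outcomes are repeated without them as a sensitivity analysis.
- Add glucose-lowering treatment (yes/no) to the insulin-resistance and beta-cell models.

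Report the number of users of each kind by group, so that a reader can see where in the range above the study lies.

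The cost is wording, one or two extra covariates, and possibly a few participants lost from one secondary outcome. No new data are needed, because current treatment is already recorded, and neither eligibility nor care changes.

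### Fasting glucose is on the single confounder list for all outcomes, yet it is a component of the HOMA2 indices listed among the primary outcomes

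*Protocol*

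**What the plan says.** Section 1.3.1 of the protocol lists the primary dependent variables. After the carotid measures it adds "reverse cholesterol transport; insulin resistance and beta cell dysfunction". Section 1.3.2 names the metabolic outcomes again, as "insulin resistance indices and beta cell function (measured via serum insulin and C-peptide and calculated using HOMA2". The same section then closes with one undivided list of confounders, which includes "blood pressure, antihypertensive treatment, fasting glucose, presence of diabetes, smoking, statin use".

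Section 5 describes the models: "The relationship between IFN and other cardiovascular risk factors will be studied by multivariable linear/logistic regression". It assigns no covariates to particular outcomes and exempts none from the list. Section 3.1 states that "Blood samples will be collected fasting from the antecubital vein during patient and control study visits", so a fasting glucose paired with insulin and C-peptide can be obtained. On eligibility, section 2.2 excludes "Evidence of uncontrolled severe concomitant cardiovascular, nervous system, pulmonary (including COPD), renal, hepatic, endocrine (including diabetes mellitus", so controlled diabetes can occur in the sample.

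**The concern.** A HOMA index is built from a fasting glucose together with insulin or C-peptide. Glucose is therefore part of the outcome, not a background factor that might confound its relation to IFN. A regression that holds glucose fixed removes one of the index's components before the IFN association is estimated.

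Two outcomes at the primary level are affected. For insulin resistance, any part of the IFN association that runs through glucose is taken out, along with the insulin response that goes with it. For beta-cell function, glucose enters the index in the opposite direction, so adjustment moves the coefficient differently and can change its sign. If both indices draw on the same analyte, the two adjusted models ask nearly the same question: higher insulin at a given glucose would read as more resistance and as more beta-cell function at once.

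**Working it through.** The protocol gives no figure to reproduce. The check is algebra plus a simulation, both on the closed-form HOMA index as a stand-in for HOMA2.

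**Algebra.** Let I be insulin and G fasting glucose.

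- ln IR = ln I + ln G − ln 22.5
- ln B = ln 20 + ln I − ln(G − 3.5)

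With G held fixed, the glucose terms are constants and only ln I varies, in both indices. The IFN coefficient for either index is then the IFN coefficient for ln I at fixed glucose.

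Write a_G and a_I for the IFN effects on ln G and ln I, and γ for the slope of ln I on ln G given IFN. For ln IR:

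- without glucose as a covariate: a_I + a_G
- with ln G as a covariate: a_I − γ·a_G
- difference: a_G(1 + γ)

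For γ of zero or more, the difference vanishes only if IFN is unrelated to glucose (a_G = 0).

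**Assumed inputs (none from the documents).** Total IFN effect on ln IR 0.10 per SD of IFN; SD of ln G 0.10; SD of ln I 0.50; medians 5.2 for glucose and 8 for insulin. The share of the effect running through glucose was 0, 10%, 25% or 50%, and the residual correlation between ln I and ln G was 0, 0.3 or 0.5. Each scenario had 400,000 simulated participants. The beta-cell index was computed where G exceeded 3.6.

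**Hand check of one row.** Share 25%, correlation 0.3: a_G = 0.025, a_I = 0.075, γ = 0.3 × 0.50 / 0.10 = 1.5. The adjusted coefficient is 0.075 − 1.5 × 0.025 = 0.0375, against 0.038 in the simulation.

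**Results (IFN coefficient).**

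| Share via glucose | Correlation | ln IR, no glucose | ln IR, with ln G | ln B, no glucose | ln B, with ln G |
|---|---|---|---|---|---|
| 0 | 0 | 0.099 | 0.099 | 0.099 | 0.099 |
| 0 | 0.3 | 0.101 | 0.101 | 0.101 | 0.101 |
| 0 | 0.5 | 0.100 | 0.099 | 0.099 | 0.099 |
| 10% | 0 | 0.098 | 0.088 | 0.055 | 0.088 |
| 10% | 0.3 | 0.101 | 0.076 | 0.058 | 0.076 |
| 10% | 0.5 | 0.099 | 0.065 | 0.057 | 0.065 |
| 25% | 0 | 0.100 | 0.075 | −0.008 | 0.075 |
| 25% | 0.3 | 0.100 | 0.038 | −0.007 | 0.038 |
| 25% | 0.5 | 0.099 | 0.012 | −0.007 | 0.012 |
| 50% | 0 | 0.099 | 0.048 | −0.116 | 0.048 |
| 50% | 0.3 | 0.100 | −0.025 | −0.116 | −0.025 |
| 50% | 0.5 | 0.100 | −0.074 | −0.115 | −0.074 |

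Three things follow.

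1. In every scenario the adjusted coefficients for IR and B agree to three decimals with each other and with that for ln I.
2. The change in the IR coefficient ranges from none to a reversal of sign, depending on the assumed share and correlation.
3. The B coefficient can also reverse, for example from −0.116 to +0.048.

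**What the equality needs.** The table feeds insulin into both indices. The protocol says they are "measured via serum insulin and C-peptide and calculated using HOMA2" but not which analyte goes into which index. If C-peptide feeds the beta-cell index, its adjusted coefficient is that of ln C-peptide at fixed glucose, which need not equal that of ln insulin. The effect of adjustment on the IR coefficient does not depend on this.

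**The case against.** The strongest reply is that the protocol never says the whole list enters every model. Section 1.3.2 defines variables, section 5 assigns no covariates, and outcome-specific sets are commonly left to a statistical analysis plan, which is not at hand. The list contains both body mass index and obesity, so it may be a catalogue of candidates. It is also true that the protocol never names glucose as a HOMA2 input.

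Part of this stands: that the adjustment will be made is an inference from one common list and an unqualified statement about multivariable regression. But the point is not that covariates are missing. The protocol does classify fasting glucose as a confounder, directly after naming the HOMA2 outcomes, and makes no exception. That classification is wrong for these outcomes even if a later document repairs it. That HOMA2 needs glucose follows from how the index is constructed.

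A reader might also infer more than the documents support:

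- **That diabetes is likewise an input.** It is not. It is a glucose-defined state tied to the outcome, so adjusting for it is a milder problem and partly a matter of choice.
- **That the two outcomes necessarily collapse into one test.** This holds only if both indices use the same analyte, which the protocol leaves open.
- **That the carotid models are over-adjusted too.** Glucose and diabetes are conventional covariates for carotid outcomes. The protocol states no mediation hypothesis, and a cross-sectional design cannot separate a mediator from a confounder.
- **That participants with treated diabetes must be left out.** Their indices may partly reflect treatment, but section 1.3.2 lists diabetes as a covariate and section 3.1 follows a section that records current treatment, so this can be examined in the analysis. Restriction is a choice of target population, and the number affected is not given.

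**Conclusion.** The point holds for the HOMA2 outcomes. Followed as written, the plan adjusts an index for one of its own components, in two outcomes listed as primary. The resulting IFN coefficient describes insulin or C-peptide at fixed glucose, not insulin resistance or beta-cell function as HOMA2 defines them.

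The mechanism is structural; the size is not established. An IR coefficient of about 0.10 becomes 0.065 to 0.088, 0.012 to 0.075, or −0.074 to +0.048 when 10%, 25% or 50% of the effect runs through glucose, and it is essentially unchanged when none does. These ranges rest on assumed effects, SDs and correlations and on the closed-form index, so no single percentage of bias should be quoted for this study. Near-identity of the two models is conditional on a shared analyte.

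This should be fixed before analysis. It does not undermine the design or the carotid analyses, and the data to be collected allow the correct models to be fitted.

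**What to change.** Replace the single confounder list in section 1.3.2 with lists by outcome, and add a statement to this effect: *fasting glucose is not a covariate in any model in which a HOMA2 index is the outcome.*

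For those same models, state how diabetes is handled: a sensitivity analysis without diabetes adjustment, one restricted to participants without treated diabetes, or both. Fasting glucose and diabetes may stay as covariates for intima-media thickness, plaque and stiffness.

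The cost is one outcome-specific covariate list and one extra sensitivity analysis. A restricted analysis would use fewer participants, by a number the protocol does not allow one to estimate. No visit, sample or measurement changes.
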